# A comparison of isometric, isotonic concentric and isotonic eccentric exercises in the physiotherapy management of subacromial pain syndrome/rotator cuff tendinopathy: study protocol for a pilot randomised controlled trial

**DOI:** 10.1186/s40814-017-0190-3

**Published:** 2017-11-14

**Keywords:** Shoulder pain, Shoulder impingement syndromes, Rotator cuff, Rehabilitation

## Abstract

**Background:**

Subacromial pain syndrome (SPS) involving rotator cuff tendinopathy is a common cause of shoulder pain and disability. Evidence suggests that structured physiotherapy may be as effective as surgery in this condition with significant improvements demonstrated in trials involving scapular retraining, rotator cuff strengthening and flexibility exercises. Most published programs typically utilise isotonic concentric and/or eccentric strengthening modes. Recently, immediate analgesic effects and muscle strength gains following heavy-load isometric exercises in lower limb tendinopathy conditions have been observed. It is pertinent to ascertain whether such outcomes can be replicated in SPS/rotator cuff tendinopathy. The primary aim of this study is to establish the feasibility of undertaking a full-scale randomised controlled trial (RCT) that compares the effects of isometric, isotonic concentric and isotonic eccentric rotator cuff contractions when used as part of a semi-standardised exercise-based physiotherapy program in patients diagnosed with SPS. The secondary aim is to explore potential trends or treatment effects of the exercise intervention.

**Methods:**

Thirty-six participants diagnosed with SPS will be randomised to one of three intervention groups and undergo a one-on-one exercise-based physiotherapy intervention, involving scapular and rotator cuff muscle retraining and strengthening. Each group will utilise a different mode of rotator cuff strengthening—isometric, isotonic concentric or isotonic eccentric. Rotator cuff tendon responses to isometric loading are not yet established in the literature; hence, individualised, progressive loading will be used in this pilot study in accordance with symptoms. The intervention will involve two phases: during Phase 1 (weeks 1–6) participants undertake the active group-specific physiotherapy treatment; in Phase 2 (weeks 6–12), they undertake a progressive, but no longer group-specific exercise program. To determine feasibility, an evaluation of key study parameters including (a) ease of recruitment (rate and number as well as suitability of the assessment algorithm), (b) adherence to all phases of the exercise intervention including home program compliance and logbook completion, (c) participant non-completion (drop out number and rate) and (d) adverse events (nature and number) will be undertaken. Secondary outcomes will measure immediate effects: (i) within-treatment changes in pain perception (verbal rating scale (VRS) and shoulder muscle strength (hand-held dynamometer) as well as longer-term changes: (ii) shoulder-related symptoms and disability (Western Ontario Rotator Cuff Index (WORC) and Shoulder Pain and Disability Index (SPADI)), (iii) perception of pain (11-point numerical rating scale (NRS), (iv) shoulder muscle strength (hand-held dynamometer) and (v) perceived global rating of change score. The immediate within-treatment assessment of pain and muscle strength will be undertaken in treatments 2 and 3, and the longer term measures will be collected at the primary (conclusion of Phase 1 at 6 weeks) and secondary (conclusion of Phase 2 at 12 weeks) end-points of the study.

**Discussion:**

The findings of this pilot study will permit evaluation of this study design for a full-scale RCT.

**Trial registration:**

Australian New Zealand Clinical Trials Registry, ACTRN12616001676404

**Electronic supplementary material:**

The online version of this article (10.1186/s40814-017-0190-3) contains supplementary material, which is available to authorized users.

## Background

Shoulder disorders are a leading cause of pain and disability in our society with one in three people experiencing shoulder pain at some stage in their lives [1, 2]. Recurrence is common and symptoms are often persistent, with 40–50% of patients reporting ongoing morbidity after 6–12 months [3] and 14% after 2 years [4]. Subacromial pain syndrome (SPS) is the most common of all shoulder diagnoses reported to general practitioners [5] and has been shown to be the most prevalent upper extremity disorder seen in working populations [6].

Extrinsic factors have been proposed as causing compression and/or abrasion of the bursal side of the rotator cuff tendons, mechanically impinged between the acromion or coracoid and the humeral head [7]. This traditional model is increasingly challenged with intrinsic rotator cuff pathology considered a more likely source of symptoms [8, 9], especially as cadaver studies have shown that rotator cuff pathology occurs more frequently within the internal substance or on the joint side of the tendon [10].

Despite a rising incidence of acromioplasty surgery worldwide [11], there is ongoing debate regarding the best treatment methods for patients presenting with SPS with both surgery and conservative management producing equivocal results [12–16]. Surgical intervention in this condition is costly both at the health-system and individual level. Indeed, subacromial decompression surgery has been shown to be associated with more time off work, while physiotherapy has been shown to be more cost-effective and associated with fewer adverse events [17]. It is therefore increasingly advocated that a course of physiotherapy be undertaken before surgery is considered.

Several researchers have investigated the most effective physiotherapy approach for SPS with some evidence to suggest that a structured exercise program is most suitable [18–22]. Heterogeneity of exercise interventions along with poor reporting of exercise protocols has prevented definitive conclusions being drawn regarding the optimum exercises and exercise parameters for the treatment of this condition in both general [18, 21, 23, 24] and working [25] populations. Hanratty et al. [21], in their systematic review and meta-analysis of exercise rehabilitation in SPS, identified that those trials where significant improvements in pain and function were demonstrated involved multiple different types of exercises including scapular stability training and targeted through-range rotator cuff strengthening and flexibility exercises. The mode of strengthening has generally been either isotonic concentric and/or eccentric in published programs.

Although eccentric exercises have been much advocated for the treatment of tendinopathy, particularly in the lower limb [26], there is limited and/or conflicting evidence to show that superior clinical outcomes are achieved with eccentric loading programs compared to other types of loading in the management of Achilles and patella [27] or rotator cuff [22, 28] tendons. More recently, the effects of isometric exercises in lower limb tendinopathy have been investigated [29–31] with Rio et al. [30] demonstrating improvements in pain and strength following heavy-load isometric contractions in patella tendinopathy. There remains, however, a paucity of research into the effects of isometric exercises in patients presenting with SPS.

Given that exercise is generally accepted as beneficial in the management of patients with SPS [32] and given our increasing understanding of intrinsic rotator cuff pathology rather than extrinsic bony compression associated with this condition, it is pertinent to ascertain whether greater clinical gains can be achieved with rotator cuff rehabilitation that utilises a specific type of muscle contraction. This is of particular clinical importance if the analgesic effect demonstrated in other tendons of the body following isometric contractions [30] can be replicated in SPS, where patients are frequently severely impaired by the pain and loss of function they experience, whatever stage along the continuum of tendon pathology they may be [33–36]. Findings from a small pilot study [37] suggest that low-load isometric exercises for rotator cuff tendinopathy may positively influence pain and tendon thickness but little has been established in the literature regarding rotator cuff tendon responses to varying isometric loads. Hence, the dosage in this present study will be semi-tailored, as per clinical practice, according to pain, severity and irritability.

The primary aim of this study is to establish the feasibility of running a full-scale randomised controlled trial (RCT) that compares the effects of isometric, isotonic concentric and isotonic eccentric rotator cuff contractions when used as part of a structured semi-individualised exercise-based physiotherapy rehabilitation program in patients diagnosed with SPS. To achieve this aim, an evaluation of key parameters including (a) ease of recruitment (rate and number as well as suitability of the assessment algorithm), (b) adherence to all phases of the exercise intervention including home program compliance and logbook completion, (c) participant non-completion (drop out number and rate) and (d) adverse events (nature and number) will be undertaken and used to inform the implementation of a full-scale RCT.

The secondary aim is to offer insights into any potential trends in treatment effects observed between the groups, to explore whether faster gains in pain, strength and therefore function are achieved from either of the three exercise interventions. To achieve this aim and facilitate sample size  estimations for a full-scale RCT, data will be collected using the selected clinical outcome measures at specific study time-points, with within-treatment and pre- and post-intervention differences evaluated across the three groups.

## Methods

### Study design

This protocol describes a pilot randomised, assessor- and participant-blind, controlled trial conforming to the SPIRIT 2013 [38] recommendations for clinical trial protocols. The study flow is outlined in Fig. 1. 

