### Procedures

Patients are referred to the public hospital physiotherapy outpatient clinic by their general practitioner or orthopaedic/other specialist. Those referred to the two private clinics may be referred by their general practitioner, orthopaedic specialist or via self-referral. Potentially eligible patients will be given information about the study. If they are interested in participating, their details will be passed to the study coordinator (RK) who will contact them to undertake a telephone screening interview. If still potentially eligible, the patient information and consent form will be mailed out and an appointment made for the patient to attend the clinic for further screening. Eligibility will be confirmed through a clinical assessment (using the assessment algorithm shown in Fig. 2) undertaken by a blinded assessing physiotherapist at each site.

Since there is a possibility of baseline differences in demographics between participants recruited from the public and private sectors, block randomisation will be used to ensure that participants from each of the clinics have an equal chance of receiving any of the interventions. Once consented, participants will be randomly allocated using an off-site randomiser and computer-generated allocation sequence to one of the three exercise groups: (i) isometric, (ii) isotonic concentric or (iii) isotonic eccentric. The treating clinician will be informed by the off-site randomiser via telephone of the group each participant is randomised to just prior to the commencement of the treatment intervention. While the treating physiotherapist cannot be blinded to treatment allocation, in order to minimise bias, the assessing physiotherapist will be blinded to group allocation, and patients will not be told which intervention group they have been randomised to.

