Correction of the scapular or humeral head position (either by patient active self-correction or therapist manual correction) that improves symptoms during objective assessment tests forms the basis of treatment 1. Initial scapular “setting” exercises allow participants to develop the scapular stability required to ensure an optimal position of the glenoid, hence, a centred humeral head during shoulder motion. Scapular retraining will ideally be taught in a standing position, but since the cohort is likely to be heterogeneous, with varying scapular and humeral head static and dynamic motion deficits, alternative positions, aimed at minimising compensatory strategies, including prone and side-lie may be temporarily adopted. Though varying between individuals, in subjects with SPS, the scapular is frequently downwardly rotated and in anterior tilt [58]; thus, scapular upward rotation exercise drills including “modified shrugs” [59, 60] will be used in this phase to retrain the scapular stabilising muscles.

The rotator cuff strengthening component of the physiotherapy intervention undertaken at treatment 2 and 3 will vary between the groups in terms of the specific type of muscle contraction taught—(i) isometric, (ii) isotonic concentric or (iii) isotonic eccentric (see Fig. 3). Taught in a standardised functional standing position, shoulder at 0°, the dosage will be semi-tailored according to pain severity and irritability, and in keeping with the tendon pathology continuum model [33]. Elastic resistance band will be used for the isotonic exercises (eccentric and concentric), while a rigid band will be used for the isometric exercises to ensure a static position is maintained.

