**Fig. 3 Fig3:**
[figure not shown]
Rotator cuff strengthening exercises—between group variation, ER external rotation, IR internal rotation

Treatment 4 will address areas of relative flexibility including the thoracic spine and upper quadrant soft tissues as well as building posterior musculature. For the thoracic spine mobility exercises, retraining may be performed in varying positions, aimed at minimising compensatory strategies. Specific upper quadrant soft tissue flexibility exercises will include a bilateral anterior shoulder/chest stretch and lateral neck flexor stretches. Posterior muscle building will involve standing rows, taught and progressed at 45° and/or 90° determined by individual ability.

Throughout Phase 1, home exercises based on the treatment intervention will be given with exercise progression as per individual response to load, aiming to maximise training effects. These will be performed independently and daily, dose dependent on exercise type. Participants will be provided with an exercise manual. Figure 4 outlines the Phase 1 home exercise program for the isometric group with the programs for the concentric and eccentric groups available as supplementary material [Additional files 1 and 2].

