**Fig. 4 Fig4:**
[figure not shown]
Phase 1 home exercise program—isometric group

To standardise treatment as much as possible and since this study is primarily focussed on exercise intervention, manual therapy techniques will not be routinely used. Consistent with the usual clinical care of patients with this shoulder disorder, for individual participants who are unable to progress beyond an exercise stage without manual therapy to facilitate, this will be undertaken but kept to a minimum and recorded.

Phase 2 of the treatment intervention commences on completion of the 6-week follow-up assessment, when participants will be provided with an exercise sheet [Additional file 3] designed to progress them from 0° into range (and therefore no longer specific to one or more of the muscle contractions being evaluated in the trial). These exercises are based on the treatment intervention and home program. The patient will be instructed on how to perform the exercises that take them into a higher range of motion, focus on further strength gains and return to function. At week 9, they will attend a one-on-one check-review to ensure compliance with the exercise sheet.

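### The trial is labelled participant-blind, but participants are only not told their group; they knowingly perform one contraction type, so the participant-rated outcomes are not blinded.

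*Protocol article*

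**What the plan says.** Under Study design, the protocol article describes a "pilot randomised, assessor- and participant-blind, controlled trial". Procedures then sets out who is masked and how. The treating physiotherapist cannot be blinded, the assessing physiotherapist is blinded, and for participants the provision is that "patients will not be told which intervention group they have been randomised to". No sham, matched appearance or check of participant blinding is described.

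Physiotherapy intervention says that the strengthening taught at treatments 2 and 3 "will vary between the groups in terms of the specific type of muscle contraction taught". On equipment it says: "Elastic resistance band will be used for the isotonic exercises (eccentric and concentric), while a rigid band will be used for the isometric exercises". The Phase 1 home exercises are done daily and independently. The isometric programme is shown in Fig. 4, with "the programs for the concentric and eccentric groups available as supplementary material". It adds: "Participants will be provided with an exercise manual".

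Outcome measures lists feasibility as primary. The secondary instruments are the VRS, WORC, SPADI, NRS and GRCS, all rated by the participant, plus hand-held dynamometry.

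**The concern.** In this trial the contraction type is the intervention. A person who holds a rigid band still, or who repeatedly moves an elastic one in a taught direction, knows what treatment they are doing, whether or not anyone names the group. Not stating a label is a weaker provision than blinding, yet the design statement presents it as blinding.

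This matters for reading the secondary results. When the participant supplies the rating, the participant is the outcome assessor, and a blinded physiotherapist does not mask that rating. Under a participant-blind label, a between-arm difference in pain, disability or perceived change would be taken as protected from expectation effects when the design does not give that protection. The consequence also outlasts the pilot. The Background says the data will help with sample size estimation for the full-scale trial, and the Discussion hopes for effect sizes and better power calculations. Both the effect sizes and the blinding claim could be carried forward unexamined.

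**Working it through.** No figure in the protocol bears on this point, so there is no arithmetic to reproduce. The check is to set the label against the mechanism, and the mechanism against what participants see and do.

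1. **Label.** Study design: blind at participant level, without qualification.
2. **Mechanism.** Procedures: the group is not disclosed to the patient. The same sentence says the assessor is blinded but says of patients only that they will not be told. The mechanism is therefore narrower than the label.
3. **What the participant learns from treatment.** Physiotherapy intervention and Table 1: session 1 (scapular work) and session 4 (rows and flexibility) are common to all arms. Sessions 2 and 3 teach external and internal rotation with the arm's own contraction type. The participant performs that contraction under one-on-one instruction, so its nature cannot be hidden from them.
4. **What the equipment shows.** Isometric: rigid band. Concentric and eccentric: elastic band. The band thus separates isometric from isotonic only. The two isotonic arms differ by the movement taught, which the participant also performs knowingly.
5. **Duration of exposure.** Home exercise is daily in Phase 1, with a different programme for each arm. Phase 2 begins after the week 6 assessment and is no longer group-specific. The week 6 end-point, which the Abstract names as the primary one for the longer-term measures, therefore falls at the close of the period in which arms differ.
6. **Who rates the outcomes.**

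| Measure | Timing | Rated by |
|---|---|---|
| VRS | before and after the arm-specific set, treatments 2 and 3 | participant |
| WORC, SPADI | baseline, week 6, week 12, 6 months | participant |
| NRS (usual, current, night) | baseline, week 6, week 12 | participant |
| GRCS | week 12 | participant |
| Dynamometry | treatments 2 and 3; baseline, week 6, week 12 | tester, from the participant's maximal effort |

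Five of the six instruments are participant-rated. The VRS is the most exposed, because pain is rated immediately before and after the contractions that define the arm. Secondary outcome (i) says the isometric arm is the one anticipated to do better there.

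7. **What can remain masked.** All three arms are active exercise, and nothing in the article says that participants are told the isometric hypothesis or shown another arm's programme. Ignorance of the other arms and of the favoured hypothesis is possible. Ignorance of one's own treatment is not.

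**The case against.** The best defence is that the mechanism is disclosed. Someone who reads Study design together with Procedures learns that participant masking rests on not naming the group, and that no sham is claimed. The arms are similar active programmes with shared components, the concentric and eccentric arms use the same band, and differential expectation requires a belief that one arm is better. The consequences are also contained: feasibility is primary, the Data management and analysis section says the study is not powered for treatment effects and that inference will be cautious, and both the assessing physiotherapist and the analyst are blinded.

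Much of this stands, and it limits the point. It does not rescue the label, because disclosing a weak mechanism does not turn it into blinding.

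Three stronger readings are tempting, and the documents support none of them.

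- A reader might infer that participants know isometric exercise is favoured and that results will be biased towards it. No section says they are told, and the consent text is not available. Expectation bias is a risk here, not an established fact.
- A reader might take the caption "Phase 1 home exercise program—isometric group" as showing that arm names appear on participants' materials. It is a figure caption for journal readers; the figure and the manuals are not shown. Keeping arm names out of participant materials may already be the practice.
- A reader might try to size the bias by comparing an assumed shift with the planning effect size of 0.66. The documents give nothing on expectation bias, so such a ratio would say nothing about this trial.

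**Conclusion.** Wrong as written. The design statement claims a property that the design does not have. Participants are not told their group name but know which exercise they perform, so the VRS, WORC, SPADI, NRS and GRCS are not blinded outcomes. At most, participants are masked to the other arms and to the favoured hypothesis, and the article does not establish even that.

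The size and direction of any expectation effect are unknown and no figure should be attached. The effect on the pilot's own conclusions is small, since the primary outcome is feasibility. It bears on how between-arm trends in participant-reported outcomes are read and on which effect sizes go into the full-scale trial. The conclusion rests on the article's description of the intervention and of who rates each outcome. It does not depend on the content of the consent form or the exercise manuals.

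**What to change.** - Restate the design as: *assessor-blind; participants not told their group name*. Add *or the study hypothesis* only if the consent and participant materials make that true.
- In the analysis section, state that between-arm differences in participant-reported outcomes, and any effect sizes taken from them for the full-scale trial, are open to expectation effects.
- Optionally, add one item on perceived allocation or expectation, asked after the week 12 outcomes are completed and reported descriptively by arm as a feasibility result. Asking it at week 6 could itself prompt expectations before the week 12 measures.

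The cost is a less favourable, but accurate, blinding claim and, if the item is added, one extra question whose answers will be imprecise at 12 participants per arm. Arms, visits, sample size and the planned analyses stay as they are.
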